### Power and sample size

The primary statistical analyses will evaluate intervention effects on 7-day point prevalence abstinence. This will be done in two ways: (1) using logistic regression at 24 months, and (2) using GEE to assess intervention effects aggregating across all assessments. Based on results from our recently completed trial [15], abstinence rates in both groups are expected to increase over time along with an increasing difference between groups. Estimated abstinence at 24 months is 16% for ST and 29% in MAPS+. PASS 2020 [85] was used to estimate sample size/power for logistic regression analyses. With a sample size of 170 per group, power is ≥ 0.80 for logistic regression analyses at 24 months with alpha = 0.05 and a two-sided test. Using GEESIZE 3.1, [86] power ≥ 0.95 for GEE analysis of abstinence across all follow-ups. No adjustments to enrollment size will be needed to account for attrition as we will utilize multiple imputation to manage missing data.

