### Recruitment and participants

Participant recruitment began in December 2022. Participants (target sample size = 340) are recruited through internet advertisements (i.e., Facebook, Instagram, Google pay-per-click ads, Craigslist) and internet-based, healthcare provider or community referrals (e.g., ClinicalTrials.gov, flyers, word-of-mouth). Inclusion criteria are: (1) ≥ 18 years of age; (2) ≥ 100 lifetime cigarettes; (3) English-speaking; (4) self-report of smoking ≥ 1 cigarette in past 30 days; (5) history of cervical cancer or CIN; (6) working smartphone; (7) valid home address; and (8) reside in Florida at the time of study enrollment. Exclusion criteria are: (1) medical condition precluding NRT; (2) currently receiving behavioral or pharmacological tobacco treatment; (3) household member enrolled in the study.

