### Missing data management

To manage missing data, multiple imputation under the Missing at Random assumption will be applied using a Markov Chain Monte Carlo method [82] via PROC MI in SAS version 9.4 given the expected large numbers of non-monotonic missing data patterns and auxiliary variables (e.g., baseline measures that predict smoking status) identified via preliminary analyses. Twenty data sets will be created. For smoking status, a post hoc adjustment [83] will be applied to implement an influence of Missing Not at Random (MNAR) (i.e., missing is due to smoking). In recent publications, [84] we have applied a small-medium effect size (Cohen’s *d* = 0.35). This approach provides better parameter estimates and tests of hypotheses than does imputing missing equals smoking. Sensitivity analyses will be performed by systematically increasing the MNAR influence in *d* = 0.15 increments to the point of missing equals smoking.

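### Multiple imputation does not remove the need for an attrition allowance: the stated 24-month power of at least 0.80 holds only if nearly all 24-month outcomes are observed

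*Protocol article*

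**What the plan says.** Under Power and sample size, the planning rates are given as follows: "Estimated abstinence at 24 months is 16% for ST and 29% in MAPS" (the second figure is for the MAPS+ arm). The claim is "With a sample size of 170 per group, power is ≥ 0.80 for logistic regression analyses at 24 months", for a two-sided comparison at the 5% level. The paragraph closes: "No adjustments to enrollment size will be needed to account for attrition as we will utilize multiple imputation to manage missing data". Recruitment and participants sets the enrolment goal ("target sample size = 340"), which is exactly 2 × 170, so the power calculation treats everyone enrolled as observed at 24 months.

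Missing data management specifies multiple imputation under missing at random with 20 data sets. Imputed smoking status is then shifted toward smoking (d = 0.35), and sensitivity analyses increase the shift up to counting all missing as smoking. The section justifies its imputation method with the phrase "given the expected large numbers of non-monotonic missing data patterns". No attrition or retention figure appears anywhere in the article.

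**The concern.** The sentence makes a design decision (no allowance for attrition) and rests it on a property that imputation does not have. Under missing at random, imputation addresses bias and gives honest standard errors. By Rubin's rules, the between-imputation variance puts the information lost with the missing outcomes back into the standard error. Power is regained only to the extent that observed data predict the missing 24-month outcome.

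This is a stated rationale, so it cannot be read as detail left to an analysis plan. At stake is how a non-significant 24-month comparison would be read: as coming from a test with at least 80% power, when its actual power depends on a retention rate that the article does not state.

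**Working it through.** **Inputs** (Power and sample size): p₁ = 0.16 (ST), p₂ = 0.29 (MAPS+), n = 170 per group, two-sided alpha 0.05 (z = 1.96).

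**1. Reproduce the plan's figure, all outcomes observed.**
- Pooled: power = Φ[(p₂ − p₁ − 1.96·SE₀)/SE₁]. SE₀ = √(2 × 0.225 × 0.775/170) = 0.04529 and SE₁ = √((0.16 × 0.84 + 0.29 × 0.71)/170) = 0.04474. So (0.13 − 0.0888)/0.04474 = 0.92, and power is **0.822**.
- Wald log odds ratio: ln OR = 0.763; SE = √(1/(170 × 0.16 × 0.84) + 1/(170 × 0.29 × 0.71)) = 0.269. So 0.763/0.269 − 1.96 = 0.88, and power is **0.810**.
- Unpooled: **0.828**.

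The claim of at least 0.80 is confirmed for complete data.

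**2. Reserve before power drops below 0.80.** Smallest n per group:
- Wald log odds ratio: 166, so 1 − 166/170 = 2.4% may be missing.
- Pooled: 161, so 5.3%.
- Unpooled: 159, so 6.5%.

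Exact enumeration of the score and Wald tests gives 0.803 at 161 per group, so the 2% end is a feature of the Wald approximation.

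**3. Power under assumed missingness m.** The article gives no rate, so these values of m are assumptions. Without recovery, n = 170(1 − m). With auxiliaries explaining a share R² of the outcome variance, effective n = 170/(1 + m(1 − R²)/(1 − m)).

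| m | n, no recovery | Pooled | Wald log OR | Effective n, R² = 0.5 | Pooled, R² = 0.5 |
|---|---|---|---|---|---|
| 10% | 153 | 0.780 | 0.768 | 161.1 | 0.801 |
| 15% | 144.5 | 0.756 | 0.744 | 156.2 | 0.788 |
| 20% | 136 | 0.731 | 0.718 | 151.1 | 0.775 |
| 30% | 119 | 0.673 | 0.660 | 140.0 | 0.743 |

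**4. Simulation check of imputation itself** (20 imputations, Rubin's rules, 3,000 replicates, Monte Carlo SE about 0.008), at 10/20/30% missing:
- No predictive auxiliary: 0.763/0.731/0.661, in line with complete cases (0.765/0.737/0.676).
- Auxiliary correlated about 0.7 with the outcome (R² about 0.5): 0.805/0.747/0.739. The recovery is partial. The 20% value lies below the 0.775 from the formula, and the complete-case power in that same run was also low (0.715).

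**5. The missing = smoking end of the sensitivity range.** Both rates shrink by (1 − m). At 20% missing they are 0.16 × 0.8 = 12.8% and 0.29 × 0.8 = 23.2%, a difference of 10.4 points instead of 13. With n = 170, pooled power is **0.706**. The effect of the planned d = 0.35 shift was not computed.

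**The case against.** Several points on the other side stand and limit the size of the finding.

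- **Auxiliary information may be substantial.** The trial collects smoking status at earlier visits and every 30 days in both arms. Used in the imputation, these could raise the tolerable loss to about 10%. At 20% missing, an R² of 0.7 would give an effective n of 170/(1 + 0.2 × 0.3/0.8) = 158 and power of about 0.79. Against this, Missing data management gives baseline measures as its example of auxiliaries and does not say that the monthly data enter, and participants who drop out may miss those prompts too.
- **The article does not forecast heavy attrition.** A reader might take "given the expected large numbers of non-monotonic missing data patterns" as an admission of high loss. It counts patterns, as a reason for the choice of imputation method. A non-monotonic pattern means that a participant can return after a gap, and the 24-month outcome need not be missing.
- **The planning rates may already include a missing-data adjustment.** They are based on the team's previous trial, and the article does not say how missing outcomes were handled in them. If an adjustment is built in, the shrinkage in step 5 would be counted twice. Missing = smoking is also only the extreme of the sensitivity range.
- **The GEE analysis has more reserve.** Its power is stated as at least 0.95. It cannot be recomputed here, because the correlation and the interim rates are not given.

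None of this rescues the sentence, which rules out any need for an allowance whatever the level of attrition.

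**Conclusion.** The rationale is wrong as written. The arithmetic behind "power is ≥ 0.80 for logistic regression analyses at 24 months" is correct for complete data; the error lies in carrying that figure over to a trial with missing outcomes. Without recovery from auxiliaries, the claim fails once about 2% to 6% of 24-month outcomes are missing; with strongly predictive auxiliaries, the limit is roughly 10%.

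A reader might infer that the 24-month test has only about 70% power. The documents do not support this: it would need roughly 20% to 30% missing with little recovery, or 20% missing with all counted as smoking, and the article states no rate. Nor does it follow that the whole trial is underpowered, since the point concerns the 24-month logistic regression only, or that enrolment must rise, since the expected retention is unknown to the reader.

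**What to change.** Delete the sentence saying that imputation makes an attrition allowance unnecessary. State the expected 24-month retention and restate the 24-month power at that retention. If 80% were expected, for example: *power is 0.82 with complete data and about 0.73 at 80% retention, before any gain from auxiliary variables* (pooled formula). The 0.73 is observed-case power and should not be presented as already reflecting the imputation or the shift toward smoking. Show by a short simulation any gain claimed from named auxiliaries and the effect of the d = 0.35 shift, and say whether the 16% and 29% already include a missing-data adjustment.

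The cost is one revised paragraph, a short simulation and a less favourable stated figure. No extra enrolment is needed to make the statement true.

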### Data and safety monitoring plan

In line with other smoking cessation research conducted in this lab, [87] the PI will be responsible for all data monitoring and for compliance with all federal and institutional IRB policies and procedures for monitoring progress, safety, reporting of unanticipated problems or adverse events, and assuring actions resulting in suspension of the study are reported. All modifications to the protocol will be submitted for IRB approval. Summaries of all relevant discussions will be promptly disseminated to study personnel via e-mail, and retraining procedures will be implemented as needed. If necessary, appropriate modifications will be made in consultation with the designated program person at the James and Esther King Florida Biomedical Research Program, National Institutes of Health, or both.

All data collected will be kept confidential. Confidentiality will be protected by identifying all participants by ID numbers only, with all data stored and managed at Moffitt Cancer Center in a secure, HIPAA-compliant electronic database (REDCap). In addition, data storage, or data transfer if there is a request, will follow all Moffitt Cancer Center requirements for data security. When data sharing is requested, de-identified data files will be transferred on a password-protected and encrypted drive and will be maintained on institutional servers with appropriate antivirus software. Final de-identified data files will be maintained by the PI at Moffitt.

### Dissemination plan

Study findings will be disseminated to the scientific community through presentations at local, national, and international meetings and via peer-reviewed publications.

## Discussion

Given that cervical cancer survivors are more likely than other subgroups of cancer survivors to smoke, and that individuals with a history of CIN who smoke are at substantially elevated risk for developing cervical cancer, there is a pressing need to target these subpopulations with efficacious smoking cessation treatment. MAPS + builds on prior evidence that MAPS-based tobacco treatment is efficacious for individuals with a history of CIN or cervical cancer and meets the need for extended support for these vulnerable populations.

This study is the first to specifically target and address the smoking cessation treatment needs of individuals with a history of CIN or cervical cancer over an extended, two-year period. MAPS + is highly flexible and designed to specifically target individuals who have varying levels of motivation to quit with treatment content specifically designed to meet their unique treatment needs over an extended treatment period. If found efficacious, MAPS + is likely to represent a sustainable, low-burden and engaging approach with broad reach and dissemination potential. For example, MAPS + could be disseminated within a variety of outreach programs and community-based networks targeting individuals with a history of CIN or cervical cancer. An important strength of our study is that individuals who are not yet ready to set a quit date are eligible to enroll. Two-thirds (i.e., 67%) of participants in our prior trial reported that they were not ready to quit at the time of study enrollment, [15] highlighting the importance of engaging these individuals in tobacco cessation treatment in an acceptable way. The Wellness Program component within MAPS + allows individuals who are not yet ready to commit to quitting smoking to focus on other life issues that are particularly salient for them (e.g., stress, family issues, finances, adjustment to a cancer diagnosis, fear of developing cancer or cancer recurrence).

In summary, theoretically based, sustainable, and tailored cessation treatments for cervical cancer and CIN survivors are needed. The MAPS + intervention approach that is under evaluation in the current trial was designed to build upon promising results from our recently completed MAPS trial among individuals with a history of CIN or cervical cancer. The current novel SMS-delivered text-based treatment adjuvant holds tremendous promise to deliver high-quality, theoretically based extended treatment designed to facilitate sustained long-term abstinence. Furthermore, given that cell phone ownership is nearly ubiquitous in the US, mobile phone-based treatments are likely to have tremendous reach and may represent an ideal treatment modality for vulnerable populations.

## Data Availability

The datasets generated and/or analyzed during the current study will be available from the corresponding author on reasonable request.

## Abbreviations

CIN: cervical intraepithelial neoplasia
GEE: generalized estimating equations
HPV: human papillomavirus
MAPS: Motivation And Problem Solving
MAPS+: Motivation And Problem Solving+
MNAR: missing not at random
NRT: nicotine replacement therapy
RCT: randomized clinical trial
REDCap: Research Electronic Data Capture
SES: socioeconomic status
SRNT: Society for Research on Nicotine and Tobacco
ST: Standard treatment
